## Abstract

**Background:**

Adults with intellectual disability (ID) are physically very inactive. This study will compare two approaches to increasing physical activity in adults with ID: a lifestyle physical activity (light-moderate intensity) approach and a structured exercise (moderate-vigorous intensity) approach. The trial will compare the short-term (3-month) and long-term (9-month) outcomes and sustainability of each approach with a usual-care control group.

**Methods/Design:**

A three-arm randomised controlled trial (RCT) will be conducted. Ninety adults with ID aged 18-55 will be randomly assigned to one of three groups: 1) a lifestyle physical activity group (*n* = 30), 2) a structured exercise group (*n* = 30), or 3) a usual care control group (*n* = 30). Participants in both groups will receive a 12-week intervention delivered by exercise specialists in the community with disability service staff, after which intervention will continue for 6 months, delivered by disability service staff only. Primary outcomes are aerobic fitness, 12-hour energy expenditure, and proxy-reported everyday physical activity. Secondary outcomes include objectively assessed physical activity and sedentary behaviour, intervention compliance, functional walking capacity, participation in domestic activities, muscle strength, body composition, psychosocial outcomes, quality of life and health care costs.

**Discussion:**

The trial results will determine the effectiveness and sustainability of two approaches to increasing physical activity and exercise among adults with ID.

**Trial registration:**

ISRCTN77889248 (18 April 2012).

## Background

Adults with intellectual disability (ID) are substantially less physically active than the general community [1–3] which may contribute to preventable physical and mental health problems [4, 5]. In Australia, the proportion of adults with ID who meet national guidelines for physical activity [6] is only around half that of the general community [7]. People with ID have a right to good health and a healthy lifestyle, yet without adequate exercise and physical activity they are more likely to experience a lower quality of life and a higher level of physical and mental ill health. Failing to address these issues places an increased burden on families and carers, as well as on disability services and health systems. Such preventable health problems can increase dependency (requiring higher disability service staffing levels), add to absenteeism from disability employment, and result in premature withdrawal from the workforce and greater health care utilisation [5].

The majority of adults with ID have the potential to meet the physical activity guidelines [8–10], but people with ID need direct personal support to plan, organise, travel to and participate in physical activities. There is a ready source of such support: disability service staff who already provide daily (usually 24-hour) support to their clients. However, these staff do not usually have the skills to support physical activity and exercise of appropriate intensity and duration. Crucially, research on ‘Active Support’ from staff has shown (a) that appropriate personal support strongly increases participation in functional everyday activities by adults with ID and (b) that disability staff can be trained to provide it [11, 12].

Physical activity is an important national policy issue in Australia [13]. The objective of this project is to improve the physical activity, aerobic fitness, strength and well-being of adults with ID by increasing their everyday physical activity and exercise levels in a manner that is sustainable in the long-term. This will involve comparing two approaches to disability staff support of physical activity by adults with ID: (I) a lifestyle physical activity (light-moderate intensity [LMI] lifestyle) approach and (II) a structured exercise (moderate-vigorous intensity [MVI] exercise) approach. The effectiveness of the two strategies for increasing physical activity and exercise in adults with ID will be evaluated and compared to a usual-care control group. By contrasting two different approaches to increased physical activity we will compare the short-term (3-month) and long-term (9-month) effectiveness and sustainability of both strategies. In addition, the project will evaluate the cost-effectiveness of both strategies.

## Methods

The trial has been registered on International Standard Randomised Controlled Trial Number Register (ISRCTN77889248).

### Design

A three arm randomised controlled clinical trial (RCT) will be conducted. Exercise specialists will deliver either a 3-month LMI-Lifestyle physical activity program or a structured MVI-Exercise program. During program delivery, exercise specialists will train disability service provider staff so that they can continue the program post intervention. The trial will be conducted with the two partner organisations, which provide services to adults with ID across Sydney, New South Wales, Australia. These services include (a) staff supported accommodation in small group homes or other community-based settings and (b) sheltered employment.

Ethics approval has been obtained from Sydney University Human Research Ethics Committee (HREC 05-2011/13821). Participants and where relevant their caregiver or guardian will be provided with information sheets, and written informed consent will be obtained prior to inclusion in the study and baseline assessment. Any adverse events related to the trial will be recorded and reported to the Human Research Ethics Committee.

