##### Intervention group 3; control participants

Participants in the control group will continue with their everyday activities. They will not be involved in any physical activity interventions led by the exercise specialists.

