### Outcome assessments

All outcomes will be assessed at baseline, 3-months post-baseline and at 9-months post-baseline. Participants and assessors will be un-blinded. The primary outcome measures are aerobic fitness, energy expenditure and physical activity. Secondary outcomes include intervention compliance, participation in domestic activity, objectively assessed physical activity and sedentary time, muscle strength, functional walking capacity, health care utilisation and cost, quality of life, body composition and psychosocial measures.

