### Primary outcome measures

#### Aerobic fitness

To assess aerobic fitness a submaximal exercise aerobic fitness test will be performed. Participants will undertake up to 4 × 5-min leg cycling using an isokinetic cycle ergometer, with resistance adjusted to elicit target heart rates equivalent to 45%, 55%, 65% and 75% of age-adjusted peak heart rate. Using ACSM metabolic equations [18], power output (W) and measured heart rate at each submaximal stage will be used to estimate submaximal oxygen consumption and VO_2_peak (ml•kg•min^-1^).

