#### Health care costs

An economic evaluation will determine the cost-effectiveness of the intervention. To assess the impact on health economics carers of the adult with ID will be given a prospective diary to complete about the person’s use of health services. The diary will ask for information on the number of hospitalizations, any medical consultations (and other medical services) and any medications taken over the period.

The Health Utilities Index 2 (HUI 2) [26] is a widely used generic measure of health state utility used for economic evaluation. The scale will be administered to carers of the adult with ID.

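### Adverse events are recorded only if related to the trial, so in an open trial with a no-programme control arm the recorded events cannot fairly compare harms between arms

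*Protocol article*

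**What the plan says.** The rule closes the ethics paragraph of the Design section: "Any adverse events related to the trial will be recorded and reported to the Human Research Ethics Committee". The article has no other adverse-event provision and does not name who judges relatedness.

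Four other places bear on it:

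- Outcome assessments, on blinding: "Participants and assessors will be un-blinded".
- Outcome assessments, on timing: "All outcomes will be assessed at baseline, 3-months post-baseline and at 9-months post-baseline". No exemption is stated for controls.
- Intervention group 3, on controls: "They will not be involved in any physical activity interventions led by the exercise specialists".
- Health care costs: "carers of the adult with ID will be given a prospective diary to complete about the person’s use of health services". On its content: "The diary will ask for information on the number of hospitalizations, any medical consultations (and other medical services) and any medications taken over the period". No relatedness condition applies to the diary.

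Adverse events are not among the primary or secondary outcomes, and the Analyses section describes no comparison of them between arms.

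**The concern.** Filtering on relatedness is ordinary for what goes to an ethics committee. Here the qualifier governs recording too, so under this rule an event judged unrelated leaves no adverse-event record that could be reclassified later.

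The filter also works differently by arm. In an exercise arm an injury can be attributed to the programme or to an assessment visit. In a control it can be attributed only to an assessment visit or another trial procedure. Allocation is not concealed from participants or assessors, so whoever makes the judgement can be expected to know the arm.

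The stakes are practical. Participants are adults reported inactive for at least 12 months, one arm trains at moderate to vigorous intensity, disability staff alone continue both programmes for six months, and the Discussion looks towards wider uptake in the disability sector. Whether staff-led activity brings more injuries than usual care is a natural question, and a randomised control arm is there to help describe it.

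**Working it through.** **1. The plan's own figure.** The article gives no figure for harms. The number that matters here is 30 per arm, and its derivation reproduces. For the between-group test in a repeated-measures ANOVA, λ = f²·N·m / (1 + (m − 1)ρ). With f = 0.40, m = 3, ρ = 0.5 and N = 69, λ = 0.16 × 69 × 3 / 2 = 16.56 on 2 and 66 df, and power is 0.955. At N = 66 it is 0.945, so 69 is the smallest multiple of 3 that reaches 0.95. Then 69 / (1 − 0.23) = 89.6, which rounds up to 90.

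**2. Routes to a recorded event, by arm.**

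| Source of a trial-related event | Exercise arms | Control |
|---|---|---|
| Programme sessions | yes | no |
| Assessments at 0, 3 and 9 months (cycle test, 6-minute walk, strength tests) | yes | yes |
| Events in everyday life | only if attributed to the trial | only if attributed to the trial |

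The cycle test is not trivial: "Participants will undertake up to 4 × 5-min leg cycling using an isokinetic cycle ergometer", with a highest target of 75% of age-adjusted peak heart rate. Control counts will therefore be low, but need not be zero.

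**3. Effect of the filter.** Let p be the true proportion of participants with an event and a the share of events called related. The recorded proportion is p × a. If p is equal in both arms, the recorded difference is p(a_active − a_control), which is zero only if the attribution shares are equal. The documents give neither p nor a, so **all values below are assumptions**. Each comparison is 30 versus 30 with a two-sided Fisher test at 0.05.

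*Same true rate in both arms; 50% of active and 5% of control events called related:*

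| True rate | Recorded rate, active vs control | Expected in 30 vs 30 | P(spurious p < 0.05) |
|---|---|---|---|
| 10% | 5% vs 0.5% | 1.5 vs 0.15 | 0.003 |
| 20% | 10% vs 1% | 3.0 vs 0.3 | 0.06 |
| 40% | 20% vs 2% | 6.0 vs 0.6 | 0.41 |

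If the active share is 30% at a true rate of 40%, the counts are 3.6 vs 0.6 and the probability is 0.09.

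*True excess, 40% active vs 20% control; 5% of control events called related:*

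| Active share called related | Recorded rate | Difference (points) | P(p < 0.05) |
|---|---|---|---|
| 20% | 8% vs 1% | 7 | 0.02 |
| 50% | 20% vs 1% | 19 | 0.48 |
| 80% | 32% vs 1% | 31 | 0.90 |
| all events recorded in both arms | 40% vs 20% | 20 | 0.30 |

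The same true excess of 20 points appears as anything from 7 to 31 points. The answer depends on attribution more than on the true excess. The absolute difference can be biased either way. The ratio is inflated whenever the active share exceeds the control share.

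**4. What the diary recovers.** It captures hospitalisations, consultations, other medical services and medications in every arm whatever their cause, and the derived costs are compared with usual care. It does not capture falls, soreness or minor injuries without medical contact. It is completed by carers in an open trial and is planned for costing.

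**5. What full recording would and would not give.** With every event recorded, Fisher power at 30 vs 30 is 0.10 (10% vs 20%), 0.30 (20% vs 40%), 0.37 (10% vs 30%) and 0.71 (10% vs 40%). At 23 vs 23 it is 0.09, 0.22, 0.30 and 0.58. Zero events in 30 would still leave rates up to 1 − 0.05^(1/30) = 9.5% possible (one-sided 95%).

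**The case against.** The strongest reply is that the sentence stands in an ethics paragraph and describes what goes to the committee. It does not say that other events go unrecorded. A condensed article may leave definitions, ascertainment and causality procedures to the full protocol, and no between-arm analysis of adverse events is planned, so no planned comparison is made wrong. Much of this stands: no primary or secondary result changes. However, the article does not leave the rule out. It states one, and that rule conditions recording on relatedness. If the full protocol records all events, correcting the sentence is enough.

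A reader might also infer more than the documents support:

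- *That controls contribute almost nothing by construction.* The filter is relatedness to the trial, not to the intervention, and controls also face the cycle, walk and strength tests.
- *That excess events cannot be detected at all.* The diary would show an excess of hospitalisations or consultations.
- *That un-blinded assessors are stated to do the filtering.* The person judging relatedness is not named. Knowledge of allocation is a reasonable inference from an open trial, and no more.
- *That the low power and the 9.5% bound are faults of this rule.* They come from 30 per arm and remain after the change.

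**Conclusion.** The point holds in limited form. As written, recording depends on relatedness. In an open trial whose controls have no programme, the chance that an event is recorded differs by arm. Recorded adverse events therefore cannot fairly compare harms between arms, and the absolute difference may be overstated or understated.

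The size cannot be fixed from the documents. Under the assumed rates, equal true risk can give a spurious excess with probability from 0.003 to 0.41. A true 20-point excess can reach p < 0.05 with probability from 0.02 to 0.90, against 0.30 with full recording. These figures rest on the assumed event rates and attribution shares, and on counting participants with an event. The diary narrows the gap for events that lead to health-service use. The efficacy analyses are unaffected, so this is a cheap improvement to the safety information and not a threat to the main results.

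**What to change.** Reword the sentence in the Design section so that:

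- adverse events are recorded in all three arms over the 9 months regardless of relatedness, using the same prompts at the 3- and 9-month assessments together with the carer diary already planned;
- relatedness is classified after recording;
- events are tabulated descriptively by arm, whatever their classification;
- reporting of related events to the ethics committee stays as it is.

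The cost is a prompt at existing visits, one table and more events to log. The table should be presented as a description of harms, with no claim that 30 per arm can rule out a moderate excess.

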### Participants

Ninety adults with ID will be recruited through the disability partner organisations on a rolling schedule. Those interested in participating will be asked to complete a Physical Activity Readiness Questionnaire (PAR-Q) [14] and where concerns are identified by the PAR-Q, medical clearance will need to be obtained in order to participate in the study.

### Inclusion criteria

Participants will be included if:they have intellectual disabilitythey are aged between 18-55 yearsit is reported they have been physically inactive for the past 12 months or longerthey reside within a 1.5-hour commute to the testing sitethey are able to participate in assessments such as the 6-minute walk testthere is a signed informed consent in accordance with the ethics requirements.

### Exclusion criteria

Participants will be excluded if:they have contraindications to participating in exercise programs or outcome assessments, as advised by the primary care physician and/or ineligibility according to American College of Sports Medicine (ACSM) criteria [15].they are judged at risk of self-harm by the disability service provider care staff.

#### Randomization

Participants will be randomly assigned to one of three groups: 1) a LMI-Lifestyle intervention physical activity group 2) a structured MVI-Exercise group or 3) a usual care control group.

#### Intervention

##### Intervention group 1; lifestyle (LMI) physical activity

Exercise specialists from the University of Sydney will use the ‘Active Support’ approach [12] to promote the LMI-Lifestyle intervention. ‘Active Support’ is an evidence-based approach for the long-term support of activities of daily living (e.g., cooking), with training of disability service provider staff to provide tailored support as a central feature. Using the principles underlying active support participants in the LMI-Lifestyle group will be encouraged to engage in a total of 150 minutes per week of LMI physical activity. Participants will be supported for 1 hour (60 minutes) a week by the exercise specialist to engage in individually tailored LMI-Lifestyle activities that are enjoyable (e.g., X-Box Kinnect, swimming, television advertisement exercises) or serve a functional purpose (e.g., walking for transport, hanging out washing). The remaining 90 minutes of weekly physical activity will be supervised by disability staff, who will be encouraged to follow an activity program set out by the university exercise specialist. During the weekly session with the exercise specialist, participants will wear a multi-sensor armband, Sensewear [16] to assess exercise intensity and compliance. Disability service provider staff will participate in the planning, and where appropriate the activity during and beyond the 12-week intervention period.

##### Intervention group 2; structured MVI-exercise

Moderate-vigorous intensity exercise classes led by the university exercise specialists will take place over 12 weeks. Three to six participants will be recruited for each cohort. A MVI-Exercise session will comprise 30 to 45 minutes of cardiovascular exercise and 15 to 20 minutes of muscular strength. Sessions will be conducted three times per week. Exercise intensity will be gradually increased over the 12 week intervention period from 40%-50% of heart rate reserve to 50%-70% of heart rate reserve [17]. Exercise modes will be conducted indoors or outdoors in local community settings (partner organisation’s facilities, parks, community gyms) using a small group approach involving activities like brisk walking, jogging and calisthenics with emphasis upon enjoyable body movements. To assess exercise intensity and compliance participants will wear a multi-sensor armband, Sensewear [16], for estimation of energy expenditure, throughout the initial 12-week intervention. Participants will also wear heart rate monitors (Polar, Port Washington, NY, USA) to ensure that they are exercising in the appropriate target heart rate zone. Partner Organisation staff will participate in the exercise sessions alongside the exercise specialists and will be trained to continue these classes beyond the 12-week intervention period.

##### Intervention group 3; control participants

Participants in the control group will continue with their everyday activities. They will not be involved in any physical activity interventions led by the exercise specialists.

### Outcome assessments

All outcomes will be assessed at baseline, 3-months post-baseline and at 9-months post-baseline. Participants and assessors will be un-blinded. The primary outcome measures are aerobic fitness, energy expenditure and physical activity. Secondary outcomes include intervention compliance, participation in domestic activity, objectively assessed physical activity and sedentary time, muscle strength, functional walking capacity, health care utilisation and cost, quality of life, body composition and psychosocial measures.

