#### Functional walking capacity

Participant’s functional walking capacity will be assessed through a 6-Minute Walk Test (6MWT). Participants will be asked to walk as fast as they can for 6 minutes and if required, the participant may briefly stop. The test will be performed indoors, along a flat, hard-surfaced passageway. The total distance walked will be measured and heart rate will be recorded using a heart rate monitor (Polar, Port Washington, NY, USA). This is a well validated test for a range of populations [20].

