#### Body composition and body fat

The Innerscan Body Composition Monitor (Tanita BC-541, Tsimshatsui East, Kowloon, Hong Kong) will be used by a trained research assistant to measure the participant’s body mass and estimated percentage body fat. Height will also be measured. From the recorded information Body Mass Index (BMI) will be calculated.

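### Assessor blinding is given up for every outcome without a reason, although the VO2peak test behind the sample size is operator-run and the walk and strength tests depend on effort

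*Protocol article*

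**What the plan says.** In the protocol article, Outcome assessments sets the schedule, "All outcomes will be assessed at baseline, 3-months post-baseline and at 9-months post-baseline", and then states "Participants and assessors will be un-blinded". No outcome or visit is exempted and no reason is given. The same section names the primaries: "The primary outcome measures are aerobic fitness, energy expenditure and physical activity".

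The sections on the individual measures show where a tester has influence:

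- **Aerobic fitness (primary).** The number of stages can vary: "Participants will undertake up to 4 × 5-min leg cycling using an isokinetic cycle ergometer". The load is set according to the participant's response: "with resistance adjusted to elicit target heart rates equivalent to 45%, 55%, 65% and 75% of age-adjusted peak heart rate". VO2peak is not measured directly but derived from the same readings: "power output (W) and measured heart rate at each submaximal stage will be used to estimate submaximal oxygen consumption".
- **Functional walking capacity (secondary).** "Participants will be asked to walk as fast as they can for 6 minutes".
- **Muscle strength (secondary).** Isometric dynamometry, including maximal handgrip.
- **Energy expenditure (primary).** An armband worn on two days.
- **Physical activity (primary).** The IPAQ-ID, answered by carers.

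The Sample size section powers the trial on VO2peak. On staffing, a trained research assistant is named only for body composition ("will be used by a trained research assistant"). The article does not say who runs the cycle, walk and strength tests.

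**The concern.** Blinding of participants is impossible here, but that does not settle whether testers must know the arm. The article treats the two together and gives up both.

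The result matters most for VO2peak. Someone sets the resistance, someone determines how many of the possible stages are completed, and the estimate is built from the heart rate and power recorded. Knowledge of the arm can enter at each step. In the walk and strength tests it can enter through encouragement.

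A tester who expects the interventions to work would plausibly favour the active arms over control. If that expectation is stronger for structured exercise, the head-to-head comparison of the two interventions is exposed as well. Such a bias does not average out: a larger sample estimates the biased difference more precisely.

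**Working it through.** **1. The plan's own figure.** Inputs from Sample size: three groups (k = 3), three measures (m = 3), f = 0.40, correlation 0.5, alpha 0.05, power 0.95. For the between-group effect in a repeated-measures ANOVA,

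λ = N·m·f² / (1 + (m − 1)·ρ), with k − 1 and N − k degrees of freedom.

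- N = 69: λ = 69 × 3 × 0.16 / 2 = 16.56, power 0.9546.
- N = 66: λ = 66 × 3 × 0.16 / 2 = 15.84, power 0.9453.

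So 69 reproduces. For attrition, 69 / 0.77 = 89.6, rounded up to 90, and 1 − 69/90 = 23.3%. The sample size is not in dispute on this point. The check confirms that VO2peak is the outcome the figure rests on.

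**2. Which outcomes a tester can influence.**

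| Outcome | Source of the value | Exposure to a tester who knows the arm |
|---|---|---|
| VO2peak (primary, powers the trial) | Adjusted resistance, variable number of stages, estimate from heart rate and power | Yes, through conduct of the test and choice of usable stages |
| 6-minute walk, strength | Effort on instruction | Yes, through encouragement |
| Armband energy expenditure (primary) | Worn device | Little, mainly decisions on valid data |
| IPAQ-ID (primary) | Carer's report | Masking the tester does not help: the respondent is the carer, who is likely to know the arm |

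**3. What a bias of a given size would do.** The documents give no bias size, so a range is assumed. Take one pairwise comparison at one time point, no true difference, a two-sided 5% t test, and a bias of b standard deviations in one arm. The noncentrality is b·√(n/2) on 2n − 2 degrees of freedom. For b = 0.2 it is 0.2 × √11.5 = 0.678 at n = 23, and 0.2 × √15 = 0.775 at n = 30.

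| Assumed bias b (SD) | Error rate, 23 per arm | Error rate, 30 per arm |
|---|---|---|
| 0.1 | 6.3% | 6.7% |
| 0.2 | 10.2% | 11.9% |
| 0.3 | 16.9% | 20.8% |
| 0.4 | 26.4% | 33.2% |

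For scale, 0.2 SD is a quarter of the planned d = 0.80 (0.2 / 0.8 = 0.25). The error rate is higher at 30 per arm than at 23, so the attrition allowance gives no protection.

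**The case against.** **The cycle test leaves limited discretion.** It is submaximal, with fixed heart-rate targets and an equation. Choosing a different resistance mainly moves the participant along the same heart rate–power line. This stands in part: the test depends on the operator more than on effort, and the route for bias is narrower than in a maximal test. The number of stages completed and the choice of usable stages remain open.

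**A condensed article leaves rosters and scripts to the full protocol.** True, and their absence is not the point. The point is a stated rule that assessors are un-blinded.

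**Stronger readings that a reader might infer, and that the documents do not support:**

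- *Trainers test their own participants.* The article does not say who tests, so this is possible but not shown.
- *Familiarity inflates VO2peak in the active arms.* Assume 70 kg, heart rate = 80 + 0.5 × watts, a peak of 180 and VO2peak = 10.8 × W/70 + 7. A uniform fall of 3, 5 or 8 beats then moves the estimate from 37.9 to 38.8, 39.4 or 40.3 ml/kg/min (2% to 7%). This measures the participant's familiarity, which a masked tester would see as well. Its sign also depends on the assumed pattern. The four targets are 81, 99, 117 and 135 bpm, at 2, 38, 74 and 110 W. If a 5-beat fall at the lowest stage fades linearly to zero at the highest, the slope is (135 − 76)/108 = 0.546. Extrapolated power is then 2 + 104/0.546 ≈ 192.4 W, and the estimate falls to 36.7. Controls also repeat every test at every visit, so familiarity is not confined to the active arms. The calculation should not be used to size this point.
- *Full masking is available from existing staff.* Staff numbers, competence to run the tests and separation from delivery are not given. One research assistant, named for body composition, does not establish it.

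**Conclusion.** The point holds in a limited form. The article states, without a reason, that assessors know the arm. That rule covers the operator-run test behind the powered primary outcome and the effort-dependent walk and strength tests. It admits a bias that could be reduced at small cost, so the plan should be changed.

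The size of the bias is unknown. The error rates in the working rest on assumed biases of 0.1 to 0.4 SD and show sensitivity only. The direction, in favour of the active arms, is plausible but not demonstrated. The point concerns the cycle, walk and strength tests. It does not show that the results would be invalid, and tester masking cannot repair the carer-reported IPAQ-ID primary outcome.

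**What to change.** Amend the blinding sentence in Outcome assessments to say that participants cannot be blinded, and add three rules:

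1. A fixed encouragement script, and the same written criteria for stage progression and for ending the test, apply to every participant at every visit. The investigators set the content of those criteria.
2. VO2peak estimation, and decisions on which stages and which device data are valid, are made on files coded without arm.
3. Where the existing roster allows, the 3- and 9-month cycle, walk and strength tests are run by a staff member who did not train that participant and is not told the arm. Any unmasking is recorded.

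Rules 1 and 2 need no extra staff, visit or measurement, only a short written procedure and coded file names. Rule 3 costs scheduling effort, and the article does not show whether staffing permits it throughout. Some participants will reveal their arm, so masking of live tests will be partial. The gain for the armband is small and there is none for the IPAQ-ID. The sample size does not change.
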